## 3. Close-Out Procedures

The end of the trial is the date of the last visit of the last participant randomized which is 12 months from the baseline. Close-out will proceed in two stages: an interim period for analysis and documentation of study results and the second one would be a debriefing of participants and dissemination of study results.

## 4. Statistical Methods

The outcome of the treated carious lesion is binary, either arrested lesion or failed to arrest at 6 months follow-up and at the end of 12 months follow up visit. The outcome will be assessed at two levels: Tooth-level—the proportion of cavitated surfaces at baseline will be compared with the proportion of the surfaces arrested at each frequency of application at 6 months follow-up and the end 12 months using chi-square methods. Between three frequencies of application (annual, semi-annual, and four times a year applications) the proportion of arrested surface at 6 months follow-up and end 12 months will be compared. This comparison will be stratified by type of tooth (posterior vs. anterior) and type of surfaces (facials vs. lingual). Child-level—each child may have one or more cavitated carious surface treated with SDF. So, the per-child proportion of cavitated carious lesions at baseline treated with 38% SDF applied at different frequencies that stayed arrested throughout observation will be determined.

The regression will be modelled on the dependent variable as a percentage of the arrested carious lesion per child with another. The two sets of analysis will be done, first, the intention-to-treat set, considering all patients as randomized regardless of whether they received the randomized treatment, and second, the “per protocol” analysis set. The hypothesis that four times application of 38% of SDF superior to other frequencies (annual or semi-annual application) is accepted, only if shown to be superior using both the “intention to treat” and “per protocol” analysis sets.

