## 2. Methods

### 2.1. Study Design

This trial is designed as a randomized, controlled trial consisting of three parallel arms with an allocation ratio of 1:1:1 (Figure 1).

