### 2.6. Definition of Study Condition (Dental Caries)

A cavitated lesion is a carious lesion with a surface that is not macroscopically intact and with a distinct discontinuity or breaks in the surface integrity [33]. The tooth should be classified as stage 5 or 6 according to Modified International Caries Detection and Assessment System (ICDAS) [25].

The status of the dentinal caries lesions will be assessed by visual inspection aided by tactile detection using a Community Periodontal Index (CPI) probe. An artificial light source from the dental chair will be used. The tooth surface will be dried and a CPI probe with the tip gently passed over the entire surface of the cavity to detect and confirm the visual evidence of caries. Cavities with yellowish/brown rough wall/floor which could be easily penetrated by the probe will be diagnosed as active. Five surfaces in each posterior tooth (occlusal, buccal, lingual, mesial, and distal) and four surfaces in each anterior tooth (labial, lingual, mesial, and distal) will be assessed. Radiographic aids will not be used for the diagnosis of caries.

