### 2.8. Primary Outcomes

The primary outcome of the study is the arrest of caries. The hardness of treated cavitated surfaces of teeth on probing (periodontal probe) is an indication that a lesion is arrested. Blackish discoloration of surface/cavity alone will not be a criterion for defining the arrested caries.

The outcome assessment will be performed for all the arms at 6 months and 12 months. SDF treated cavities of teeth with arrested caries are defined as surfaces with active cavitated caries at baseline that changed into surfaces with arrested cavitated caries on subsequent assessments. The possible scenarios and their assessment are as follows:Any teeth with treated carious lesions that are lost due to exfoliation will be considered arrested throughout the lifetime of the tooth. For any reason, if the child’s teeth are restored before the trial period, censoring of the data depends on the duration of the trial period the child has participated.The following dental complications due to the evolution of caries will not be considered as caries arrested.○The teeth extracted due to caries progression.○If the SDF treated cavities, caries progressed beyond the dentine.○If the tooth is extracted due to fracture, trauma will not be counted for the study.

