### 2.11. Sample Size

The sample size was calculated based on the primary objective. In an exploration study [26], those children treated weekly with 38% SDF had a slightly higher proportion of arrested caries compared to annual application. There was no considerable difference in the proportion of caries arresting by either semiannual or annual application (less than 10%). We expect that the proportion of the arrested carious lesion not to be more than 14% between the two frequencies of application. Considering a slightly higher proportion of caries arrest by the four times application as compared to others, we estimated the sample size at the power of 0.80 and alpha error of 0.05 to be 120 per arm. Being a population (tribal), which is not mainstream and owing to the demands of multiple follows of the tribal population, it is expected that we could encounter a lost-to-follow-up of about 30%. Accordingly, the final sample size has been increased to 160 children per arm. In total, 480 children will be enrolled on the trial.

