### 2.12. Study Implementation

The 2–6-year-old children visiting the primary health care center (Amrita Kripa Health Care Centre) for routine dental/medical care or accompanying parents requiring dental/medical care will be invited to be a part of the study. On dental examination, if the child is found to satisfy the inclusion criteria, then the parent of the child will be given the option for treating the carious lesion by SDF treatment or by routine restoration. If the parent opts for SDF treatment for the child, then an option to participate in the trial will be given. If the parent agrees, then the consenting process is followed. Informed consent in the local language will be obtained from willing participants.

The selected child for trial will be randomly allocated to one of the three intervention arms as per computer-generated randomization sequence stratified at 40% type of tooth (anterior) and 50% gender. In this process, stratification is performed by gender (males, females) and type of primary tooth (anterior, posterior), so will have a total of 4 strata (2 by 2). Treatment assignments are then made from separate computer-generated randomization lists created in advance for each stratum. This randomization sequence will be generated from a remote site independent from the knowledge of the Principal Investigator (PI).

The randomization will be completed by a trial coordinator based on the computer-generated randomization sequence. The randomization list will remain with the trial coordinator until the completion of the study. The intervention (SDF application) will be performed by the PI and outcome assessment will be performed by two investigators other than the PI. Due to the obvious nature of the treatment neither the investigator performing the treatment, nor the study participant can be blinded. However, the outcome assessors are proposed to be blinded.

Allocation concealment will be conducted using opaque sealed envelopes (sealed sequentially numbered envelops irreversibly) containing codes (corresponding to the randomization list). The allocation concealment will be performed by one author (RV). The allocation sequence will not be disclosed to the PI until the completion of the study.

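### The tooth-level chi-square counts surfaces as independent although children are randomised, so its type I error can exceed 5%, and the superiority rule does not say which level of analysis decides

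*Protocol article*

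**What the plan says.** The trial has "three parallel arms with an allocation ratio of 1:1:1" (section 2.1), and the unit of randomisation is the child: "The selected child for trial will be randomly allocated to one of the three intervention arms" (section 2.12).

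Section 4 plans two levels of analysis. At tooth level, baseline cavitated surfaces are set against "the proportion of the surfaces arrested at each frequency of application at 6 months follow-up and the end 12 months using chi-square methods". The next sentence turns to the three application frequencies and says that "the proportion of arrested surface at 6 months follow-up and end 12 months will be compared"; it names no test. That comparison is then to be stratified by tooth type and by surface type.

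At child level, the section notes that "each child may have one or more cavitated carious surface treated with SDF". It therefore plans a per-child proportion arrested and a regression on the percentage arrested per child.

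Superiority of the four-times schedule is accepted only if it is shown in both the intention-to-treat and the per-protocol sets. The rule does not say whether the tooth-level or the child-level result is meant.

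**The concern.** A chi-square test on pooled surfaces takes every surface as an independent observation. Surfaces in one mouth share diet, plaque and attendance, so they tend to arrest or fail together.

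The protocol's own rules add correlation within a tooth. Section 2.6 assesses "Five surfaces in each posterior tooth (occlusal, buccal, lingual, mesial, and distal) and four surfaces in each anterior tooth", and section 2.8 scores some events for the whole tooth: "Any teeth with treated carious lesions that are lost due to exfoliation will be considered arrested throughout the lifetime of the tooth". Extraction for caries progression counts as not arrested. All treated surfaces of such a tooth therefore move together.

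If surfaces are correlated within the child and the test ignores it, standard errors are too small, intervals too narrow and p-values too low. Section 2.8 defines arrest on surfaces, so this test bears directly on the primary outcome. Nothing in section 4 marks its result as descriptive or keeps it from supporting a superiority claim.

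**Working it through.** **The plan's own figure.** In section 2.11, "we estimated the sample size at the power of 0.80 and alpha error of 0.05 to be 120 per arm", counted in children. The section gives a 14-point difference but no base arrest rate, so 120 cannot be reproduced from its stated inputs. With an assumed 0.75 against 0.89, two-sided, the usual two-proportion formula gives 118. The closed-form check below does not depend on this number.

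**Inputs.** Alpha is 0.05 (section 2.11), taken here as two-sided. Surfaces per child (m) and the within-child intraclass correlation (ICC) are not in the protocol. Both are assumed over a range.

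**Formulas.** With equal m:

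- Design effect: DE = 1 + (m − 1) × ICC. Standard errors are understated by a factor of √DE.
- True type I error of a nominal 5% pairwise test: 2 × (1 − Φ(1.96/√DE)).
- True type I error of a nominal 5% three-arm chi-square (2 degrees of freedom): exp(−5.991/(2 × DE)).

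**Worked case, m = 3, ICC = 0.3.** DE = 1 + 2 × 0.3 = 1.6. Pairwise: 1.96/√1.6 = 1.55, giving 12.1%. Three-arm: exp(−5.991/3.2) = 15.4%.

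| m | ICC | DE | Pairwise | Three-arm |
|---|---|---|---|---|
| 1 | any | 1.0 | 5.0% | 5.0% |
| 2 | 0.05 | 1.05 | 5.6% | 5.8% |
| 2 | 0.1 | 1.1 | 6.2% | 6.6% |
| 2 | 0.3 | 1.3 | 8.6% | 10.0% |
| 2 | 0.5 | 1.5 | 11.0% | 13.6% |
| 3 | 0.1 | 1.2 | 7.4% | 8.2% |
| 3 | 0.3 | 1.6 | 12.1% | 15.4% |
| 3 | 0.5 | 2.0 | 16.6% | 22.4% |
| 5 | 0.1 | 1.4 | 9.8% | 11.8% |
| 5 | 0.3 | 2.2 | 18.6% | 25.6% |
| 5 | 0.5 | 3.0 | 25.8% | 36.8% |

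For m = 2 to 5 and ICC 0.1 to 0.5, √DE runs from √1.1 = 1.05 to √3 = 1.73.

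**Simulation check.** Beta-binomial data with no true difference, 120 children per arm, an assumed arrest rate of 0.70 and 4,000 runs per setting:

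- The three-arm surface chi-square rejected in 6.4% (m = 2, ICC 0.1), 15.8% (m = 3, ICC 0.3) and 36.0% (m = 5, ICC 0.5) of trials, in line with the formula.
- With uneven counts (one plus a Poisson number, mean 3 or 4 surfaces) it rejected in 9.4% to 35.6%.
- One proportion per child, compared by one-way analysis of variance, rejected in 4.4% to 5.8% across all settings.
- A false win for four times over annual (nominal 2.5%) occurred in 2.8%, 6.2% and 12.9% in the same three settings. A false win over both other arms occurred in 0.7%, 1.7% and 4.6%, against 0.4% to 0.5% with one surface per child.

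**The case against.** **The between-arm sentence names no test.** This is correct: chi-square for the arm comparison is an inference. It is the natural one, because the sentence follows directly under the same tooth-level heading and no other tooth-level method is named. Confining chi-square to the preceding sentence would not rescue it, since the test would then compare the baseline and follow-up states of the same surfaces, which are not independent either.

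**The child-level regression may be what decides.** That reading is reasonable. The superiority rule stands in the same paragraph as the regression, the intention-to-treat set is defined by patients, and the sample size counts children. A child-level analysis respects the unit of randomisation. What remains is that the rule names no level, so a favourable surface-level p-value is not excluded. Requiring both analysis sets does not cure the clustering, because the same unadjusted test could be run in both.

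**The size is unknown.** This stands in full. A reader might infer that a false finding of superiority is far likelier than 5%. The documents do not support that. They give neither m nor ICC, the inflation is slight at m = 2 and ICC 0.05, and the main figures count any false rejection in either direction. The error for beating annual alone passes 5% only with moderate clustering. The error for beating both comparators stayed below 5% in every setting simulated, although it rose with clustering.

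**Conclusion.** The point holds in a conditional form. On its natural reading, the tooth-level arm comparison and its strata rest on a test that ignores correlation within the randomised child. A method is stated and it does not suit the data described, so this is not merely detail left to an analysis plan.

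The direction is certain whenever children contribute more than one surface and the ICC is positive: false rejection above the nominal 5%. The size, about 7% to 37% for three arms and 6% to 26% for one pair, rests on the assumed m = 2 to 5 and ICC 0.1 to 0.5. It vanishes if m = 1 or ICC = 0. The child-level regression is not affected; the gap there is only that it is not named as decisive.

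**What to change.** In section 4:

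1. Compare the arms at surface level with a method clustered on the child: logistic GEE with robust standard errors, a logistic model with a random child effect, or a Rao-Scott chi-square.
2. Obtain tooth-type and surface-type results from arm-by-type interactions in that model, or from clustered analyses within each stratum. Main-effect terms alone would give one adjusted arm effect, not the planned stratified comparisons.
3. State which analysis decides superiority, the child-level regression or the cluster-adjusted surface analysis, and that unadjusted surface proportions are descriptive.

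The cost is wording and standard software, with no new data and no extra children. The downside is wider surface-level intervals and larger p-values.

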### 2.7. Interventions

#### Silver Diammine Fluoride

SDF is a colorless liquid containing silver ionic particles. It contains 38% (44,800 ppm) fluoride ion at a pH of 10. This formulation constitutes 25% silver, 8% ammonia, 5% fluoride, and 62% water. One drop (0.05 mL) of 38% SDF solution (2.24 F-ion mg/dose) is required for the treatment of one tooth. The SDF treatment protocol consists of removing gross debris from the cavitated tooth, drying the affected area, isolating the tooth with the help of cotton rolls and suction, placing a small amount of SDF on the affected area, gently drying the SDF for 1 min, removing excess SDF with cotton gauze and isolating the tooth for up to 3 min [34]. This procedure will be performed after the tooth is removed of debris (with the aid of a toothbrush) and soft caries using a spoon excavator. It includes gross debris from cavitation to allow better SDF contact with denatured dentin. Carious dentin excavation before SDF application is not necessary. As excavation may reduce the proportion of arrested caries lesions that become black, it may be considered for esthetic purposes. No rotary instruments will be used for caries removal.

The study participants will be allocated into one of the three parallel arms who will receive 38% SDF application as follows:
Study arm 1: annually (once a year; baseline visit);Study arm 2: bi-annually (twice a year at 6-month intervals; baseline visit and after 6 months);Study arm 3: four times a year (baseline visit, 2nd, 4th, and 8th week).

In the baseline visit in all the study arms, the child will be assessed for cavitated caries lesions and caries risk (ADA Caries Risk Assessment Form (Age 0–6)). After obtaining consent for the trial, SDF is applied on the selected caries teeth depending on the study arm. The demographic characteristics, plaque index, and caries status will be assessed. In the subsequent visits depending on the study arm, SDF will be applied (Table 1).

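### The child-level measure of continuous arrest cannot credit lesions first arrested by arm 2's second application, and at 6 months arms 1 and 2 have had identical treatment

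*Protocol article*

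**What the plan says.** The schedules are in section 2.7 of the protocol article (Silver Diammine Fluoride):

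- "Study arm 1: annually (once a year; baseline visit").
- "Study arm 2: bi-annually (twice a year at 6-month intervals; baseline visit and after 6 months").
- "Study arm 3: four times a year (baseline visit, 2nd, 4th, and 8th week").

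Table 1 places arm 2's second application at the 6-month visit, where the first follow-up outcome assessment also takes place. Section 2.8 sets the assessment times: "The outcome assessment will be performed for all the arms at 6 months and 12 months". It describes arrested cavities as "surfaces with active cavitated caries at baseline that changed into surfaces with arrested cavitated caries on subsequent assessments".

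Section 4 treats the lesion outcome as binary at each of the two visits and then sets out two levels of analysis. At tooth level, across the three frequencies, "the proportion of arrested surface at 6 months follow-up and end 12 months will be compared". At child level, the per-child proportion of treated lesions "that stayed arrested throughout observation will be determined". The regression that follows takes the percentage of arrested lesions per child as its dependent variable, without a time point. The hypothesis is that four applications are superior to the other frequencies.

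**The concern.** There are two linked difficulties.

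First, arm 2 differs from arm 1 only through the application given at 6 months. A lesion that is active at the 6-month assessment and arrested at 12 months has not been arrested throughout, so the child-level measure scores it as a failure. Section 2.8 would count it as arrested at 12 months. Arm 3's applications are complete by week 8, so any arrest they achieve by month 6 can count. The measure therefore leaves out one way in which the semi-annual schedule could work, and it leans towards the arm that the protocol hypothesises to be superior.

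Second, the 6-month comparison is planned on the same footing as the 12-month one. At 6 months the semi-annual arm is, in treatment received, a second annual arm.

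The primary objective is to compare these three frequencies. At stake is whether the child-level result can show what a second application adds, and whether a 6-month difference between arms 1 and 2 is misread as an effect of frequency.

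**Working it through.** **1. Treatment received before each assessment** (section 2.7 and Table 1)

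| Arm | Before the 6-month assessment | Before the 12-month assessment |
|---|---|---|
| 1 | 1 application | 1 application |
| 2 | 1 application | 2 applications |
| 3 | 4 applications | 4 applications |

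At 6 months the expected difference between arms 1 and 2 is zero by design.

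**2. What each definition counts**

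Let p6 be the proportion of lesions arrested at 6 months, s the probability that an arrested lesion stays arrested to 12 months (retention), and r the probability that a lesion active at 6 months is arrested at 12 months (late conversion).

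- Arrested throughout: p6 × s
- Arrested at 12 months: p6 × s + (1 − p6) × r

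The two differ by (1 − p6) × r in each arm. Arms 1 and 2 share the same expected p6, so the part of the arm 2 minus arm 1 difference that the first definition loses is

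(1 − p6) × (r2 − r1),

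where r2 and r1 are late conversion with and without the second application.

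**3. Size**

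The protocol states no figure for this point, and p6, s, r1 and r2 are not given, so there is nothing to reproduce. All rates below are assumptions. Each pair is arm 1 against arm 2.

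| Case | p6 | s | r | Arrested throughout | 12-month status | Lost |
|---|---|---|---|---|---|---|
| Second application only converts | 60% | 90% / 90% | 5% / 40% | 54% / 54%, difference 0 | 56% / 70%, difference 14 | 14 |
| It only maintains | 60% | 80% / 95% | 5% / 5% | 48% / 57%, difference 9 | 50% / 59%, difference 9 | 0 |
| Both | 60% | 85% / 95% | 5% / 40% | 51% / 57%, difference 6 | 53% / 73%, difference 20 | 14 |
| Both, higher p6 | 70% | 85% / 95% | 5% / 40% | 59.5% / 66.5%, difference 7 | 61% / 78.5%, difference 17.5 | 10.5 |

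First row in full: 0.60 × 0.90 = 0.54 in both arms. Late conversion adds 0.40 × 0.05 = 0.02 in arm 1 and 0.40 × 0.40 = 0.16 in arm 2, giving 0.56 and 0.70. The formula agrees: (1 − 0.60) × (0.40 − 0.05) = 0.14.

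The loss ranges from 0, when the second application only maintains arrest, to 14 points in these cases. For scale, section 2.11 plans on a difference of at most 14%, read here as percentage points.

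**4. The 6-month comparison**

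Inputs: 120 children per arm and 14 points (section 2.11), two-sided alpha of 0.05 (sidedness is not stated), arms 1 and 2 equal, arm 3 higher by 14 points, and one independent binary outcome per child. Base rates of 50%, 60% and 70% are assumed.

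At 60% against 74%, the overall proportion is (0.60 + 0.60 + 0.74)/3 = 0.647.

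- Three-arm chi-square, 2 df: non-centrality 120 × [2 × 0.0467² + 0.0933²] / (0.647 × 0.353) = 6.86; power 65%.
- Arm 3 against arms 1 and 2 pooled (120 against 240), 1 df: null SE = √[0.647 × 0.353 × (1/120 + 1/240)] = 0.0534; alternative SE = √[0.74 × 0.26/120 + 0.60 × 0.40/240] = 0.0510; z = (0.14 − 1.96 × 0.0534)/0.0510 = 0.69; power 76%.

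| Base rate | Three-arm test | Arm 3 against arms 1 + 2 |
|---|---|---|
| 50% | 61% | 72% |
| 60% | 65% | 76% |
| 70% | 73% | 84% |

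A separate comparison of arm 1 with arm 2 at 6 months would reject only at the alpha rate.

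**The case against.** The strongest reply is that the child-level measure is one of several and need not decide the trial. The tooth-level comparison at 12 months counts late conversion, and the regression's dependent variable is not tied to continuous arrest. That stands, and it limits the damage. It does not repair the child-level measure, and the regression's missing time point leaves open which definition it would use.

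It can also be said that sustained arrest is a legitimate target, and that early arrest from front-loaded applications is a real feature of arm 3. That is fair as a reason to report the measure. It is not a reason for it to stand as the child-level comparison of frequencies when section 2.8 defines arrest without requiring it at every visit.

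Two readings would soften the point. If throughout meant from first arrest onward, late conversions would count. If section 2.8's plural assessments meant every later visit, the two definitions would agree, though the tilt against arm 2 would remain. The text says neither.

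Stronger conclusions are tempting but not supported:

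- A reader might infer that the measure cannot credit the second application at all. It can: a lesion arrested at 6 months and kept arrested to 12 months counts, as the maintenance-only case shows.
- A reader might infer that the 6-month three-arm test is empty. It is not, because arm 3 differs. Section 4 also does not write out a separate annual against semi-annual test at that visit.
- A reader might take the whole of arm 2's late conversion as the distortion, 0.40 × 0.40 = 16 points in the first case. That is gross, because arm 1's late conversions are lost too; the net figure is 14.
- A reader might infer an inflated error rate from many pairwise tests. Section 4 does not state unadjusted pairwise tests, and multiplicity is commonly left to an analysis plan that is not shown here.

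**Conclusion.** The point holds in a limited form. The child-level measure credits the second application for maintaining arrest but not for late conversion. That tilts it against arm 2 and puts it at odds with section 2.8. The 6-month comparison informs on arm 3 against the other two arms and cannot separate annual from semi-annual application.

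The schedule facts rest on the protocol alone. The size does not: the loss in the arm 2 against arm 1 contrast is (1 − p6) × (r2 − r1), and the 14-point illustration depends on assumed rates. If the second application mainly maintains arrest, the loss is near zero. The 6-month power figures also rest on assumed base rates and ignore clustering of lesions within children.

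A valid 12-month tooth-level comparison is already planned, so this should be fixed before analysis but does not undermine the trial as a whole.

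**What to change.** Change the analysis wording in section 4 as follows:

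- Define the child-level outcome as the per-child proportion of treated lesions arrested at 12 months, using the section 2.8 definition and its rules for lost, restored and extracted teeth. Use the same quantity as the regression's dependent variable.
- Name 12 months as the primary time point for comparing frequencies.
- Keep the proportion arrested at both visits as a descriptive measure.
- At 6 months, compare arm 3 with arms 1 and 2 pooled, as a secondary analysis. State that a 6-month difference between arms 1 and 2 is not to be read as an effect of frequency.

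This needs no extra visits or children and no change to the treatment schedule. Continuous arrest already required the 12-month visit, so no new data are needed. The small cost is that 6-month results become secondary.

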There have been multiple clinical trials and several systematic reviews reporting the application of SDF causing the arrest of caries lesions in a high percentage of cases (30–70%) [16,17,18,19,20,21,22,23,24]. Nearly 70% of caries lesions in primary teeth would be expected to be arrested in two years after SDF application with the variation of annual or biannual application as compared to combined controls of 5% NaF varnish or restorations. According to the AAPD manual [25], nearly 68% (95% CI = 9.7 to 97.7) of cavitated caries lesions in primary teeth would be expected to be arrested in two years after SDF application with a variety of annual or biannual application as compared combined controls of 5% Sodium fluoride (NAF) varnish or restorations. The American Dental Association (ADA) guidelines recommend the use of 38% SDF twice a year application over 5% NaF varnish (once per week for 3 weeks application) to arrest the cavitated caries coronal lesions in primary and permanent teeth [16]. However, it is a conditional recommendation that implies that not all patients would benefit from the intervention and depends on individual risk for caries, preferences, values, etc.

Studies are comparing various frequencies (thrice a year, weekly, biannual, annual, five times weekly per year, etc.) of SDF; however, the evidence is inconsistent. A clinical trial has shown that the yearly application of SDF has a higher proportion of arrested caries compared to the weekly application [26]. Biannual application of SDF was found to be superior compared to annual application in arresting cavitated carious lesion [27,28,29,30,31]. Annual application of silver diamine fluoride prevented many more carious lesions than application of fluoride varnish four times per year [26,31].

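### Child-level prognostic measures are collected at baseline, but no planned analysis names one as a covariate, and the regression sentence that could carry them is incomplete

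*Protocol article*

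**What the plan says.** Baseline data. Under section 2.7 (Silver Diammine Fluoride), at the first visit in all arms "the child will be assessed for cavitated caries lesions and caries risk (ADA Caries Risk Assessment Form (Age 0–6"), and further "The demographic characteristics, plaque index, and caries status will be assessed".

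Analysis. Section 4 works at two levels.
- **Tooth level.** Chi-square is the only test named. The comparison between the three frequencies is stratified by anterior or posterior tooth and by facial or lingual surface.
- **Child level.** The proportion of treated lesions that stay arrested is determined for each child, and then "The regression will be modelled on the dependent variable as a percentage of the arrested carious lesion per child with another". The sentence ends there.

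Randomisation. Section 2.12 stratifies by gender and tooth type, giving four strata. Gender is not mentioned again in section 4.

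Size. Section 2.11 states "we estimated the sample size at the power of 0.80 and alpha error of 0.05 to be 120 per arm". It also says "it is expected that we could encounter a lost-to-follow-up of about 30" per cent, and that "the final sample size has been increased to 160 children per arm".

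**The concern.** Children will differ in plaque, caries risk and number of open lesions, and these may affect whether lesions arrest. Any such variation that is not modelled stays in the residual and widens the interval for each between-arm difference. The two tooth-level stratifiers describe the lesion and do not capture differences between children. The outcome's own baseline value cannot help either: every treated lesion is active at the start, so percentage arrested is zero for every child.

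The design has little power to spare. Section 2.11 expects only a slight advantage for four applications and substantial loss to follow-up. Section 4 accepts superiority only if both the intention-to-treat and the per-protocol sets show it, so the chance of success cannot exceed the lower of the two powers.

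There is also a risk to credibility. As published, the regression sentence would be compatible with almost any right-hand side, so covariates could be chosen after the data are seen.

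**Working it through.** **Inputs from the article.** Power 0.80, alpha 0.05 (sidedness not stated; two-sided assumed), 120 evaluable and 160 enrolled per arm, loss about 30% (all section 2.11).

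**Input not in the article.** R², the share of variance in percentage arrested that the baseline measures explain. It is assumed, and a range is shown.

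**Step 1: the plan's own figure.** Section 2.11 gives a gap ("We expect that the proportion of the arrested carious lesion not to be more than 14% between the two frequencies of application") but no pair of arrest proportions, so 120 cannot be reproduced directly. With the usual two-sided, uncorrected formula for two proportions and a 14-point gap:

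| Assumed proportions | n per arm |
|---|---|
| 68% vs 82% (68% is the two-year figure in the Introduction) | 149 |
| 74% vs 88% | 123 |
| 75% vs 89% | 118 |

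The stated 120 is matched only near 74–75% versus 88–89%. The rest of the working takes the stated 0.80 at 120 per arm as given.

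**Step 2: effect of adjustment.** The planned non-centrality is 1.960 + 0.842 = 2.802. Adjustment multiplies the residual variance by (1 − R²), so

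power = Φ(2.802 / √(1 − R²) − 1.960).

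The number per arm that would then give 0.80 is 120 × (1 − R²).

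| R² | 2.802/√(1 − R²) | Power at 120 per arm | n per arm for 0.80 |
|---|---|---|---|
| 0 | 2.802 | 0.80 | 120 |
| 0.05 | 2.875 | 0.82 | 114 |
| 0.10 | 2.954 | 0.84 | 108 |
| 0.20 | 3.133 | 0.88 | 96 |

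**Step 3: at the attrition the protocol expects.** 160 × 0.70 = 112 evaluable per arm. The non-centrality becomes 2.802 × √(112/120) = 2.707, and unadjusted power is Φ(2.707 − 1.960) = 0.77. With adjustment it is 0.79 at R² = 0.05, 0.81 at 0.10 and 0.86 at 0.20. An R² of about 0.10 would therefore recover the planned level.

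**Limits.** The formula suits the child-level percentage. For binary surfaces it is only a rough guide, and it does not deal with clustering of surfaces within a child, which is a separate matter.

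**The case against.** **A covariate list is normally left to the SAP.** This stands as far as it goes: a missing list is not an error in a journal article. But the article does state an analysis, and the regression it states cannot be carried out as written because not even arm is named. The point is to complete and improve a stated method.

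**The regression may have covariates.** A reader might infer that the investigators chose a model without baseline predictors. The text does not support that. The sentence is incomplete, so it shows neither inclusion nor exclusion.

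**The surface analysis is not simply unadjusted.** This stands in part. The between-arm comparison is stratified by two lesion-level factors, and the sentence announcing it names no test of its own; chi-square appears in the sentence before. Section 4 does not say whether the strata are pooled into one adjusted test or only reported separately. A stratified chi-square method could also take a categorical child-level factor such as risk category, but none is named.

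**The gain is unknown and may be small.** This stands. Sections 1 and 6 describe the whole population as at high caries risk. Section 2.5 limits lesions to ICDAS 5–6 and excludes pulpal involvement. A restricted range of risk and severity makes the lower part of the R² range more plausible.

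**Unadjusted comparison of randomised arms is valid.** This is also correct. The issue is efficiency and pre-specification, not bias.

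**Conclusion.** The point holds as a modest, nearly free improvement. Child-level prognostic measures are collected, section 4 names none of them as a covariate, and the one model that could use them is left unfinished.

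If the stated 0.80 at 120 per arm is taken as right, pre-specified adjustment adds about 2 percentage points of power at R² = 0.05, 4 at 0.10 and 8 at 0.20. It adds essentially nothing if the measures are not prognostic. These sizes rest entirely on the assumed R².

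It would go too far to say that the trial forfeits a known amount of power: the article contains no correlation between any baseline measure and arrest.

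**What to change.** Complete the regression sentence in section 4 before unblinding, along these lines:

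- **Outcome:** percentage of treated lesions arrested per child.
- **Model terms:** arm as the factor of interest; gender and tooth type, as used in the randomisation strata; plaque index, ADA caries-risk category, number of treated cavitated surfaces and age, all measured at the baseline visit.
- **Inference:** robust standard errors, with each adjusted between-arm difference reported with its 95% CI.
- **Support:** keep the unadjusted comparison alongside. The tooth-level analysis can stay; the child-level model need not replace it as the sole main analysis.
- **ICDAS stage:** add it only if it is recorded for each lesion. The article gives stage 5–6 as an eligibility class and does not say that the stage is kept lesion by lesion.

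The cost is one or two sentences, a simple rule for missing baseline values, and a few degrees of freedom out of about 336 to 360 analysed children (3 × 112 to 3 × 120). The listed covariates need no new visits, staff or measurements.
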